##### Qualitative interview

All interviews will be semi-structured. Guides for individual interviews with students and school nurses contain 4–5 predetermined themes with follow-up questions, and permit an open dialog. Students are interviewed about their experiences with the 8^th^-grade consultation, relation to the school nurse, health literacy, quality of life, and coping. School nurses' individual interviews touch upon their experiences with coping during the 8^th^-grade consultation, student relations, and how to identify and follow up students with additional needs.

The guide for focus group interviews with school nurses is made with the opportunity to add themes related to implementation after preliminary quantitative data analyses (see mixed-methods). The complete interview guide covers themes such as experiences with the 8^th^-grade consultation, collaboration with school, national guidelines, implementation of the elements, and determinants for implementation. School personnel are interviewed on three main topics regarding the nature, content, and quality of collaboration with school health services. In addition, they are asked about experiences with implementing SchoolHealth and relevant implementation determinants.

#### Mixed-methods (iii)

A mixed-methods experimental design (convergent and sequential [24]), from a pluralistic and meta-paradigmatic perspective [25], will be used to investigate experiences with the different implementation elements and the complexity of implementation mechanisms across conditions. We will corroborate quantitative and qualitative data on the value of, and experiences with, the implementation elements and the guideline recommendations. Qualitative data will provide a more in-depth understanding of findings from different viewpoints. According to Teddlie and Tashakkori [26], mixed methods research involves seeing qualitative and quantitative data as two different ends of a continuum, where one moves seamlessly across it to pursue optimal answers to the different research questions of the study. This means that the different data sources will be given different weights and priorities throughout the analytical process to best answer the research question. Thus, the sequential dimension of the design will include conducting preliminary analyses of quantitative data about implementation determinants, fidelity, and collaboration after each data collection wave to inform themes and questions for the qualitative interviews.

#### Student data and national data registers (iv)

We will compare baseline data from GuideMe on health and health service use with cross-sectional data from wave 4 of the adolescent part of the Nord-Trøndelag Health Study (Young-HUNT Study) [27], a Norwegian population-based study in Central Norway [28, 29]. In the Young-HUNT wave 4 survey there were 8066 (76% of the invited) 13–19-year-old participants. Data from GuideMe and Young-HUNT4 will also be linked with national registry data on healthcare service use, such as The Norwegian Registry for Primary Health Care (KPR) and the Norwegian Patient Registry (NPR) [30].

Health and health service use among participants in both studies will be assessed and compared. Subgroup analyses will be conducted to test whether demographics (e.g., gender, socioeconomic status, schools) affect associations between health measures (e.g., mental health, medical conditions, health behavior).

### Outcomes

The study uses the Exploration, Preparation, Implementation, and Sustainment Framework (EPIS) [31] as a theoretical framework for investigating implementation as multilevel processes influenced by innovation factors, the outer and inner implementation context, and the interplay between factors (i.e., bridging factors) across four phases of implementation [32]. Due to the highly autonomous and individual nature of school nurses' practice settings, we complement EPIS with the Capabilities, Opportunities, and Motivation model of Behavior change (COM-B) [33]) to inform explorations of how and why implementation strategies influence school nurses' fidelity to guidelines. EPIS and COM-B have informed the development of studies' theories of change and hypotheses for how the implementation strategies influence fidelity to guidelines and guideline effects (see Fig. 2 for logic model). EPIS has informed measurements of organizational and individual-level implementation determinants and focus group interviews. COM-B has informed measures of individual-level determinants of behavior change and individual interviews.

**Fig. 2 Fig2:**
[figure not shown]
Logic model depicting a simplification of the theorized relationships between the guideline recommendations, implementation elements, determinants, and proximal and medial outcomes

The outcomes are operationalized and described in Table 3 by measurements, data collection method, informant, and timepoint. Details about the measurement instruments, including psychometric properties and validations, are in Supplementary file 1.

**Table 3 Tab3:** Outcomes and measures, measurements, method of data collection, informant, and timepoint for each measure in the factorial experiment

Outcome/measure	Measurement	Method of data collection ^a^	Informant ^b^	Timepoint		
				**T1**	**T2**	**T3**
**Implementation Outcome**						
*Fidelity to guidelines – 8*^*th*^*-grade consultation*						
Adherence to guidelines	Self-developed	Quant	N, S		x	
Dosage	Self-developed	Quant	N		x	
Quality in using guidelines	Self-developed	Quant + Qual	N, S		x	x
Adaptations to guidelines	Self-developed	Quant + Qual	N		x	x
*Fidelity to guidelines – Collaboration, schools and school health service*						
Collaboration-adherence	Self-developed	Quant	N, T	x		x
Dosage	Self-developed	Quant	N	x		x
Quality in collaboration	Self-developed	Quant	N, T	x		x
Adaptations to guidelines		Qual	N			x
**Health and Service Outcomes**						
*Identification of vulnerable students*		Qual	N			
Mental health*	SDQ	Quant	S	x		x
Student function	Self-developed	Quant	N		x	
Follow-up group	National classification		N		x	
Follow-up consultation(s)	Self-developed	Quant	N			
Somatic symptoms	CSSI-8	Quant	S	x		x
Quality of Life	KIDSCREEN-27	Quant	S	x		x
Self-efficiacy*	GSE-5	Quant	S	x	x	x
Health literacy	HLSAC	Quant + Qual	S	x	x	x
Health behaviors	Self-developed	Quant	S	x		x
School environment and attendence	Self-developed, items from similar studies	Quant	S	x		x
User satisfaction*	Partly self-developed	Quant + Qual	S		x	
Work-related self-efficiacy*	GSE-5, slightly adjusted	Quant + Qual	N	x		x
Interprofessional collaboration	Interprofessional collaboration	Quant	N, T	x		x
**Determinants**						
Implementation climate	ICS	Quant + Qual	N, L	x		x
Implementation leadership	ILS	Quant + Qual	N, L	x		x
Implementability of guidelines	FIM, AIM, IAM	Quant + Qual	N, L	x		x
Fidelity to implementation elements (adherence, adaptations, and quality)**	Self-developed	Quant + Qual	N, L, P	**	**	**
Implementation capacity		Qual	N	x		
Satisfaction with implementation elements	Self-developed	Quant + Qual	N, T, S			x
Background variables	Self-developed	Quant	N, T	x		
Demographics	Self-developed	Quant	S	x		

*Abbreviations*: *SDQ* Strengths and Difficulties Questionnaire, *CSSI-8* Children’ Somatic Symptoms Inventory, *GSE-5* General Self-Efficacy Scale, *HLSAC* Health Literacy for School-Aged Children, *ICS* The Implementation Climate Scale, *ILS* The Implementation Leadership Scale, *FIM* Feasibility of Intervention Measure, *AIM*  Acceptability of Intervention Measure, *IAM* Intervention Appropriateness Measure

^*^Both determinant and health/service outcome

^**^ Fidelity to implementation elements is monitored throughout the study

^a^Quant: Quantitative digital survey. Qual: Qualitative interviews

^b^N = School nurse, L = Leaders school health services, T = Teachers/School leaders, S = Students, P = Project staff

#### Implementation outcomes (proximal)

Fidelity to guidelines will be assessed through items encompassing the three constructs adherence to guidelines, adaptations to guidelines, and quality in using guidelines. *Adherence to guidelines* is conceptualized as adhering to specific key recommendations for how to carry out the 8^th^-grade consultation and collaboration with schools. Measurement of 8^th^-grade consultation adherence include items about whether health information was adapted to the student, and focus on habits important to promote good health. Additionally, checklist items about themes addressed and registering height and weight also index adherence. Collaboration adherence is measured with questions about how the collaboration is organized (formal and informal meetings), whether school nurses participated in any of the schools' planning hours or meetings, and topics on which the school and school nurses are supposed to collaborate and how they collaborate.

The *dosage* of 8^th^ grade consultation will be measured by the time used on the consultation, and the dosage of collaboration by the number of scheduled meetings.

*Quality in using the 8*^*th*^*-grade consultation guidelines* is indexed by post-consultation measures of school nurses’ and students’ perceptions of their alliance and achievement of the guidelines' core functions, such as empowerment, reinforcement of positive health behavior, and identification of follow-up needs. *Quality in using collaboration guidelines* is indexed by measuring perceptions of achievement of the core functions of collaboration guidelines, such as common values and understanding, role and responsibility clarification, ease of contact with each other, knowledge about each other's competence and regulations, mutual respect, and structure.

School nurses report *adaptations to consultation* through open-ended questions in the post-consultation questionnaire (T2). Adaptations will be retrospectively coded by using the Framework for Reporting Adaptations and Modifications to Evidence-based Implementation Strategies [34], labeled fidelity-consistent (positive) or fidelity-inconsistent (negative). The labeling will be based on a qualitative judgment of whether the adaptation was likely to maintain the core function of the recommendation in our theory of change (fidelity-consistent) or not [35]. The qualitative judgment will also be informed by the measures of quality. Qualitative interviews with school nurses and school personnel will explore adaptation to collaboration guidelines.

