## Abstract

**Background:**

Norwegian school health services received a national best-practice guideline in 2017. To promote healthy life skills and identify adolescents needing support, the guideline includes strong recommendations for individual consultations with all 8th graders and increased collaboration with schools. To help implement the recommendations, a blended implementation strategy (SchoolHealth) was co-created with school nurses, students, and stakeholders. SchoolHealth consists of three implementation elements: Digital dialog and administration tool (audit and feedback +), Dialog support (external consultation), and Collaboration materials (targeted dissemination). This hybrid study will test the main and combined effects of the elements on guideline fidelity and effectiveness.

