**Methods:**

The GuideMe study is a factorial cluster randomized controlled trial examining SchoolHealth's effectiveness on guideline fidelity and guideline effectiveness goals. Forty Norwegian secondary schools will be randomized to eight different combinations of the elements in SchoolHealth. Participants will include school nurses and school personnel from these schools, and 8^th^ grade students (*n* = *1200).* Primary outcomes are school nurses' fidelity to the guidelines and student's ability to cope with their life (i.e., health literacy, positive health behaviors and self-efficacy). Quantitative methods will be used to test effects and mechanisms, while mixed- and qualitative methods will be used to explore mechanisms, experiences, and other phenomena in depth. Participants will complete digital questionnaires at the start and end of the schoolyear, and after the consultation during the schoolyear. The study will run in two waves, each lasting for one school year. The multifactorial design allows testing of interactions and main effects due to equal distribution of all factors within each main effect. Sustainment and scale-up of optimized SchoolHealth elements using national infrastructure are simultaneously prepared.

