#### Audit and feedback + (Digital Feedback and Administration Tool [DFA])

DFA is the only element that involves the students directly. School nurses/teachers administer a digital health information form to students before their 8^th−^grade consultation. The topics in the form are based on the recommended topics in the guideline. Filling out a health form may empower students through preparing topics they can bring up in the consultation and the opportunity to reflect upon topics important to them. The school nurse will receive an *individual feedback report*, with the main aim to support school nurses in tailoring consultations to individual needs, thus increasing nurses' capability, opportunity, and motivation to use the 8^th^-grade consultation recommendations. It may also help identify students in need of additional support and follow-up. After the 8^th^-grade consultation, the students and the school nurses answer questions regarding the consultation. The students report user satisfaction, including relation with the school nurse and involvement in consultation, generating the *user satisfaction report*. The school nurse and the students answer questions about the content of the consultation (fidelity to guideline), generating the *8*^*th*^*-grade consultation report*. Both reports will be available for the school nurse and their service leaders on the DFA platform. Additionally, the DFA platform include a *school report*, an aggregated summary based on all the students' pre-consultation health information forms. Here, school health nurses and leaders can compare their schools/districts aggregated answers with that of others in the study. The school report covers topics highlighted in the guideline recommendations on which the school health service and schools should collaborate.

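### Consultation fidelity is defined only for consultations that were held; the share of students consulted is not named as a component, although consulting every 8th grader is the recommendation

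*Protocol article*

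**What the plan says.** The protocol article's abstract states that "the guideline includes strong recommendations for individual consultations with all 8th graders", and the Background section repeats this. The abstract also states: "Primary outcomes are school nurses' fidelity to the guidelines and student's ability to cope with their life". Research question 1 asks for the elements' effects on fidelity to the consultation recommendation and to the collaboration recommendation.

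The section on proximal implementation outcomes sets out the content: "Fidelity to guidelines will be assessed through items encompassing the three constructs adherence to guidelines, adaptations to guidelines, and quality in using guidelines". For the consultation part:

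- **Adherence** "is conceptualized as adhering to specific key recommendations for how to carry out the" consultation. The examples are tailored information, focus on health habits, themes covered, and height and weight.
- **Dosage**: "grade consultation will be measured by the time used on the consultation".
- **Quality** "is indexed by post-consultation measures of school nurses" and of students.
- **Adaptations** are reported by nurses "through open-ended questions in the post-consultation questionnaire (T2").

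The section on the digital tool says that, once the consultation is over, "the students and the school nurses answer questions regarding the consultation". Table 3 places consultation adherence and dosage at T2 only, and quality and adaptations at T2 and T3. Collaboration fidelity is measured at T1 and T3. Table 3 also has a row for follow-up consultations, but that counts later contacts, not whether the 8th-grade consultation took place.

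**The concern.** Each consultation measure takes a held consultation as its starting point. As defined, a nurse who sees half of the class thoroughly can score above one who sees the whole class a little less thoroughly, although the second is closer to what the guideline asks.

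Table 1 has consultations running through the semester while the elements are in use, so being consulted is a post-randomisation event. The elements could plausibly move it in either direction. The digital tool has an administrative function that might help nurses reach more students. Dialog support and Collaboration materials ask for time that might otherwise go to consultations. The article does not say that either happens.

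If coverage or case mix does differ, a comparison of content scores among consulted students is no longer a comparison of the randomised groups. The questions on how effects relate to fidelity (2ii and 3ii) are touched as well, because students who were never consulted have outcomes at T1 and T3 but no defined consultation-fidelity value.

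**Working it through.** **The plan's own figure.** Inputs from the power section: α = 0.05 (two-sided assumed), d = 0.30, power 0.80, ICC 0.05, mean cluster size 30 with SD 15 (CV = 0.5).

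- Per factor level without clustering: 175, so 350 in total.
- Design effect: 1 + ((0.5² + 1) × 30 − 1) × 0.05 = 2.825.
- Normal approximation: 350 × 2.825 = 989 students, or 33 schools.
- Noncentral t for one main effect, df = schools − 8: power 0.796 at 35 schools and 0.808 at 36. So 36 × 30 = 1080 students, as stated.

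The stated size reproduces. The point does not depend on it; d = 0.30 serves below only as a yardstick.

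**Is coverage named?** Setting the outcome text beside Table 3:

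| Component | Definition | Timepoint | Can it register a consultation not held? |
|---|---|---|---|
| Adherence | how it is carried out | T2 | not as defined |
| Dosage | time used | T2 | not as defined |
| Quality | post-consultation ratings | T2, T3 | not as defined |
| Adaptations | post-consultation report, interviews | T2, T3 | not as defined |
| Collaboration dosage | number of scheduled meetings | T1, T3 | yes, a count can be zero |

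The last row shows that the article uses a count where collaboration is concerned, but not for the consultation.

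**Could the elements plausibly matter for coverage?** Table 1 gives Dialog support 3 × 180 + 60 = 600 minutes of meetings and encourages 5 × 60 = 300 minutes for Collaboration materials. At 30 minutes per consultation these equal 20 and 10 consultations, against an average of 30 students per school. This shows only that the time is not negligible.

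**Size, under assumed inputs.** The documents give no coverage rate, so everything below is illustration.

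*(a) Sign.* Score 0–100 among consulted students; the all-student score is coverage × score, with unconsulted students at 0.

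- Coverage 95% vs 80%, score 70 vs 75: conditional +5.0; all students 0.80 × 75 − 0.95 × 70 = 60 − 66.5 = −6.5.
- Coverage 80% vs 95%, score 70 vs 68: conditional −2.0; all students 0.95 × 68 − 0.80 × 70 = 64.6 − 56 = +8.6.

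*(b) Selection with no true effect on content.* Let ρ be the correlation between the standardised score and the propensity to be seen. Among the share c who are seen, the mean shifts by ρ × φ(z_c)/c, where φ is the standard normal density and z_c is the c-quantile. The spurious contrast is the difference of the two shifts.

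| Coverage without vs with element | ρ = 0.2 | ρ = 0.5 |
|---|---|---|
| 95% vs 95% | 0 | 0 |
| 95% vs 85% | +0.03 | +0.08 |
| 90% vs 70% | +0.06 | +0.15 |
| 70% vs 95% | −0.08 | −0.19 |

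For example, 90% vs 70%: φ(z)/c is 0.195 and 0.497, a gap of 0.302; 0.302 × 0.2 = 0.06 and 0.302 × 0.5 = 0.15. In absolute size the non-zero entries run from 11% to 65% of 0.30.

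*(c) Power.* The loss from fewer records is minor: with 40 schools, power is 0.85 at full coverage, 0.82 at 80% and 0.80 at 70%.

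**The case against.** Several counter-arguments have force.

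- **Unseen material.** The examples of adherence items are not presented as a full list, and instrument detail is placed in Supplementary file 1, which is not shown. A coverage item could be there. This stands and lowers confidence. It does not remove the point, because the article's own definitions of adherence and dosage concern held consultations.
- **Scope.** A reader might infer that the whole primary outcome ignores coverage. The documents do not support that. Collaboration fidelity is measured without any consultation, and health literacy, self-efficacy and health behaviours are measured at T1 and T3 whether or not one was held, so an effect of coverage on students can still appear there.
- **Timing.** A reader might also infer that all consultation fidelity is collected only at T2. Table 3 marks quality and adaptations at T3 too; only adherence and dosage are T2-only.
- **Analysis set.** The article does not say that students without a T2 form are excluded. Such handling belongs to an analysis plan and is not criticised here.
- **Aim.** The elements' listed targets are mainly tailoring, self-efficacy, involvement and identification of needs, not numbers seen. Measuring how consultations are done is a defensible choice. It is still only part of fidelity to a recommendation about all students.
- **Recoverability.** Consultations must be entered in the student's health record, and school health service use is to be linked from the national primary care register. Coverage is probably obtainable, but neither source is named as a fidelity measure.
- **Magnitude.** Nothing in the documents shows that coverage will differ, and the direction of selection could go either way.

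**Conclusion.** The point holds for the consultation part of fidelity. As the article defines it, this part describes only consultations that took place, and it names no measure of how many students were reached. That gap exists whatever coverage turns out to be.

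Bias is a separate and conditional matter. It arises only if the elements change how many or which students are seen, and it is zero if neither differs by condition. Under assumed coverage gaps of 10 to 25 points and correlations of 0.2 to 0.5, selection alone gives 0.03 to 0.19 SD. The sign reversals in the illustration depend on chosen inputs and on scoring unconsulted students as 0. They show what can happen, not what is expected. No stated number is wrong, and the sample size need not change.

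It should be fixed, with moderate confidence.

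**What to change.** - For every consented student, record by T3 whether the 8th-grade consultation took place (yes/no and date), taken from the nurse's existing record. Do not infer it from a missing T2 form.
- Name coverage, the share of consented students consulted, as a component of consultation fidelity. Compare it by condition over all consented students and report it beside the content scores. State that it describes consented students in the classes that schools chose, not all 8th graders.
- Label adherence, dosage and quality among consulted students as conditional on a consultation.
- An all-student score with unconsulted students at 0 can be a sensitivity analysis. It should not be required as the primary score: it puts a spike at zero into an outcome planned for linear mixed models, and it penalises nurses for students who were absent or declined.
- The article appeared after the 2022/23 wave, so the field for that wave would come retrospectively from the records. The mixed-methods section foresees preliminary fidelity analyses after each wave, so the change should be dated and should say what had been seen by then.

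Cost: one field per student, about 30 per school and 1200 in all, and one more fidelity component to report.
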